### Data Collection

Trial data is collected and entered into the eCRF system PheedIt provided by Clinical Trials Office (CTO), Center for Clinical Cancer Studies (CKC), Karolinska University Hospital. eCRFs are required to be completed for each subject enrolled in the trial and all continuously collected data will be entered in the eCRF in a timely manner, within 1 month. All data must be entered in English. The PI is responsible for ensuring the accuracy, completeness and legibility of the data recorded in the eCRFs. Study monitors, data manager or the study statistician will review data according to the Monitoring Plan and Data Management Plan. Queries that are sent to site will require response and confirmation or correction of the data by delegated site staff. The Data Management Plan provides detailed information about data collection and data management throughout the trial.

### Data Quality and Monitoring

The source documents consist of the medical records and any additional relevant documentation for trial purpose. This documentation will contain trial information such as trial number, date of informed consent, trial assignment and the name of the trial PI.

Source data for all variables will be defined in a source data log, which will be stored in the Investigator's Site File. Specific trial information such as trial title, trial number, date of informed consent, trial treatment and that the patient adheres to the inclusion and exclusion criteria should be recorded in the medical record.

### Site Set-Up and Initiation

Prior to site activation of each participating site must have an Investigator Site File with all essential documents in place, including authority approvals, Clinical Study Site Agreements and a signed delegations log. Key members of the site research team will be required to attend either a meeting or a teleconference covering aspects of the trial aim and design, protocol procedures, Adverse Event reporting, collection and reporting of data and record keeping.

### Trial Monitoring

The trial quality will be assured by trial monitoring in accordance with ICH-GCP of the trial sites in all participating countries. The monitoring will be carried out in accordance with the risk assessment and a common Monitoring Plan prepared by the monitoring unit in Sweden. At least three monitoring visits will be performed; the site initiation visit, a visit after the first included patient and a close-out visit. Additional on-site monitoring visits or more extensive source data verification may be triggered for example by poor CRF return, poor data quality, low/high SAE reporting rates, excessive number of patient withdrawals or deviations. The data recorded in the eCRFs will be controlled for consistency with the source data/hospital records during the monitoring (source data verification). Any discrepancies of data will be documented and explained in the monitoring reports.

### Audit and Inspection

The Investigator and site staff will permit trial-related monitoring, audits, ethical review, and regulatory inspection(s) at their site, providing direct access to source data/documents.

### Statistical Analysis Plan

The sample size calculation is based on a Simon Two Stage Minimax design and the primary outcome measure of response rate assessed by the Revised International Neuroblastoma Response Criteria at 1 month after completion of therapy (42, 43). A complete response + partial response rate of 40% or more is defined as the acceptable level of response. A response of 20% or less would be considered unacceptably low. The probability of obtaining a false negative result, β (i.e., incorrectly rejecting for further study a treatment with a true response rate of ≥ 40%) is set at 20%. The probability of obtaining a false positive result, α (i.e., incorrectly accepting for further study a treatment that has a true response rate ≤ 20%) is set at 10%. Stage 1 requires 14 eligible and evaluable patients, with a minimum of 3 to be responders to proceed to stage 2. A further 10 patients will be recruited in Stage 2. A minimum of 8 responses out of 24 patients would be considered success and indicate that the treatment is active and should go onto further studies to evaluate efficacy (while taking account of toxicity). A standard Simon 2 stage has been chosen over a single stage (e.g., A'Hern) design in order to allow the trial to be stopped sooner, and to prevent unnecessary exposure of patients to radiotherapy, if insufficient responses are seen. Simon Optimal (3 responses /12 patients after first stage, 8/25 at end) and Minimax (3/14, 8/24) designs gives very similar numbers, so the decision to choose the latter is largely arbitrary (one patient fewer in total, but slightly more conservative after first stage). Sample size calculations were performed using Sample Size Tables for Clinical Trials software by Machin and Campbell. Loss to follow-up is likely to be minimal; all patients are referred from clinicians at established oncology centers with excellent close relations and regular communication or the patient's continued care is at the recruiting hospital. In addition, it is current standard practice to follow-up patients until they are 18 and then refer them to adult late effect physicians (according to long term follow-up guidelines from Children's Cancer and Leukemia Group (CCLG) and other relevant guidelines).

### Analysis

Response to treatment is assessed using the Revised International Neuroblastoma Response Criteria (INRC). Overall response is defined as complete response, partial response, minor response, stable disease, or progressive disease. Baseline assessment is carried out within 2 months prior to registration and an additional ^68^Ga-DOTATOC PET/CT is performed within 2 weeks prior to treatment. Response evaluation is performed 1 month and 4 months post treatment. Overall response integrates tumor response in the primary tumor, soft tissue and bone metastases, and bone marrow. Primary and metastatic soft tissue sites are assessed by MRI or CT, ^68^Ga-DOTATOC PET/CT and ^123^I-mIBG imaging. Target and non-target lesions are defined and scored according to the RECIST 1.1 guidelines. Assessment of bone marrow involvement is done by evaluation of bilateral aspirates and bilateral trephine biopsies from a total of four sampled sites. The analysis of the primary outcome measure is carried out on an eligible and evaluable patient basis. Patients who are registered, but for any reason did not complete treatment and/or the first response evaluation at 1 month after EOT, are deemed not evaluable, and so will be excluded from the primary analysis. Outcomes for all patients will be reported on an intention-to-treat basis. Descriptive statistics are used to summarize baseline characteristics, treatment, report harms, and response outcomes.

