Pilot studies on pediatric patients, performed by Gains et al. at the University College London Hospitals NHS Trust, UK (UCLH) and by Kong et al. the Royal Children's Hospital, Melbourne, Australia (RCH) have shown that ^68^Ga-DOTATOC or DOTATATE PET/CT is a feasible method to identify patients with neuroblastoma that can benefit PRRT with ^177^Lu-DOTATATE. Both of these studies reported promising results from treating children with refractory or relapsed neuroblastoma with ^177^Lu-DOTATATE, some of which achieving remission that lasted for several years (39, 40). A phase IIa LuDO trial at UCLH, did not, however, show an objective response among 14 evaluable patients (41). In this study, dose limiting toxicity was observed only in one patient and the investigators speculate that this may have been due to concurrent use of myelosuppressive antibiotics, rather than an actual side effect of the trial treatment. The measured renal radiation dose was lower than the objective in all cases and the median value was only about 70% of the 23 Gy objective. The main reason for this was the rapid disease progression in many of the study subjects, indicating that with an intensified dosing schedule, the administered activity could have been substantially increased in most patients. Despite the negative result, the investigators conclude that ^177^Lu-DOTATATE may have value as a treatment for neuroblastoma and propose further clinical trials to be conducted (29). The design of the LuDO-N Trial, described in this paper, builds on the experience of the recent LuDO-Trial.

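### Treated children who miss dose 2 or the 1-month evaluation are dropped from the primary analysis; if they are replaced, the 10% false-positive rate is not guaranteed

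*Protocol article*

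**What the plan says.** The Statistical Analysis Plan section of the protocol article fixes the design: "The sample size calculation is based on a Simon Two Stage Minimax design". The two reference rates are given as "A complete response + partial response rate of 40% or more is defined as the acceptable level of response" and "A response of 20% or less would be considered unacceptably low". The false-positive probability is set at 10% and is defined in terms of the treatment's true response rate being 20% or less. The false-negative probability is 20%.

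The first decision is tied to evaluable patients: "Stage 1 requires 14 eligible and evaluable patients, with a minimum of 3 to be responders to proceed to stage 2". Ten more follow in stage 2, and at least 8 responses in 24 count as success.

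The Analysis section puts the primary outcome on eligible and evaluable patients. Registered patients who "did not complete treatment and/or the first response evaluation at 1 month after EOT, are deemed not evaluable, and so will be excluded" from that analysis, whatever the cause. The same section says that outcomes for all patients will also be reported by intention to treat, with no decision rule attached.

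On missing data, the Statistical Analysis Plan section says "Loss to follow-up is likely to be minimal" and gives referral links and routine follow-up practice as the reason.

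**The concern.** Evaluability depends on what happens after treatment starts. A child who receives dose 1 and then progresses, dies or stops for toxicity before dose 2, or who does not reach the 1-month assessment, is a treatment failure. Under this rule the child is not counted as one. A child who progresses but receives both doses and is assessed does stay in, as progressive disease. The problem is therefore confined to failures early enough to prevent dose 2 or the assessment.

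Some such loss is foreseeable. The Introduction says of the kidney dose shortfall in the predecessor trial: "The main reason for this was the rapid disease progression in many of the study subjects". The Discussion expects more myelotoxicity from the short interval between doses. The reassurance about loss to follow-up concerns contact with families, not failure of treatment.

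The decision rules were calibrated to 20% and 40%. Removing failures raises the response rate among those who remain, so an inactive schedule is more likely to pass stage 1 and to be called active. That would weaken the stated purpose of the two stages, which is to stop early and spare children exposure when responses are too few.

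**Working it through.** **Inputs from the article (Statistical Analysis Plan section).** Stage 1: n1 = 14, continue with at least 3 responders. Final: n = 24, success with at least 8. Reference rates 0.20 and 0.40; limits 10% (false positive) and 20% (false negative).

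**Input that is assumed.** A share q of patients is excluded, and all of them are non-responders. The article gives no value for q, so a range is shown.

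**Step 1: reproduce the design.** With response probability p,

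P(success) = Σ over x = 3,…,14 of P[Bin(14, p) = x] × P[Bin(10, p) ≥ 8 − x]

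P(stop at stage 1) = P[Bin(14, p) ≤ 2]

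- p = 0.20: P(success) = 0.0874; P(stop) = 0.448
- p = 0.40: P(success) = 0.8024

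Both error limits are met. A search over designs returns 3/14 then 8/24 as the minimax design, and 3/12 then 8/25 as the optimal one, as the article states. The sample size arithmetic is correct.

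**Step 2: exclusion with replacement.** If the rate among all patients is 0.20 and the excluded share q contains no responders, the rate among evaluable patients is 0.20/(1 − q). For q = 10% this is 0.20/0.90 = 0.2222. Putting this rate into the Step 1 formulas, with 14 and 24 evaluable patients reached:

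| Excluded q | Evaluable rate | False-positive rate | Stop at stage 1 |
|---|---|---|---|
| 0% | 20.0% | 8.7% | 44.8% |
| 2% | 20.4% | 9.6% | 43.3% |
| 5% | 21.1% | 11.1% | 40.9% |
| 10% | 22.2% | 14.2% | 36.8% |
| 20% | 25.0% | 23.0% | 28.1% |

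Solving for a false-positive rate of 10% gives q ≈ 2.8%. An expected loss of one patient in 25 (q = 4%) gives 10.6%.

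**Step 3: no replacement.** Suppose only 14 and then 24 patients are registered and the counts 3 and 8 stay fixed. An excluded non-responder then cannot add to the count, and the false-positive rate stays at 8.7%. If the final rule is instead read as one third of the evaluable patients, still without replacement, the rate is 12.3% at q = 10% and 20.5% at q = 20%.

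**Step 4: which reading applies.**

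- Statistical Analysis Plan section: stage 1 needs 14 eligible and evaluable patients, which implies replacement. The 8 in 24 rule does not repeat the word evaluable.
- Study Design and Setting: 14 patients are recruited in stage 1.
- Planned Interim Analysis and Timelines: the interim follows inclusion of the first 14.

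These three statements do not agree on what 14 means.

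**Step 5: power if failures are counted.** If the 40% target was meant for evaluable patients, the rate among all treated is 0.40 × (1 − q).

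- q = 10%: 0.36, power 67.4%
- q = 20%: 0.32, power 51.4%

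Both compare with 80.2% when 40% applies to all treated patients.

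**The case against.** A reader might infer that the 10% error rate is simply lost, and that all early progressors and deaths vanish from the analysis. The article does not support either reading.

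- **Replacement is never stated.** It is implied by the stage 1 wording and put in doubt by two other sections. Without it, and with fixed counts, there is no inflation. This stands, and the conclusion has to be conditional.
- **The excluded share is unknown.** The predecessor trial gave activity every 2 months over 6 months. Here two doses 2–4 weeks apart and an assessment 1 month later take about 6–8 weeks, and entry requires a life expectancy above 3 months. Nothing in the article points to 20% or more, and at 2% the limit still holds. This also stands, although the margin is thin.
- **The calculation is a worst case.** Not every excluded patient need be a treated non-responder; some may never have been dosed, and leaving those out is far less of a concern.
- **Early failures remain visible.** All outcomes are reported by intention to treat, and progression-free and overall survival run from registration. Success leads only to further studies. This softens the reporting, but neither go/no-go rule is attached to those results.
- **Counting failures may cost power.** This is right if 40% was set with evaluable patients in mind, and it belongs in the decision.

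**Conclusion.** The point holds in conditional form. The exclusion rule takes some treated failures out of the set on which response is judged, while the stated false-positive rate refers to the treatment's true response rate. If excluded patients are replaced to reach 14 and 24 evaluable, and all of them are non-responders, the 10% limit survives only while about 2.8% or fewer are excluded. Beyond that, the table under Step 2 gives the size for each assumed share.

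The inflation rests on both assumptions, and the article confirms neither. What it does establish is the rule itself, its lack of any exception for treatment failure, and the disagreement between three sections about what 14 counts. The 3/14 and 8/24 design is correctly derived; the fault lies in the population to which it is applied.

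**What to change.** 1. Define the primary set as all eligible patients who receive any 177Lu-DOTATATE.
2. Count progression, death, withdrawal for toxicity or no 1-month assessment as non-response.
3. Apply 3/14 and 8/24 to that set, without replacing treated patients. For the all-treated response rate, the exact false-positive rate is then 8.7% and power 80.2%.
4. Keep the evaluable-only rate as a sensitivity analysis.
5. State that 20% and 40% refer to all treated patients.
6. Reconcile Study Design and Setting, Statistical Analysis Plan, and Planned Interim Analysis and Timelines on whether 14 means recruited or evaluable.

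The cost is a change of wording, and the planned 24 patients stay. The reported response rate will be somewhat lower. If the sponsor did mean 40% for evaluable patients only, power falls as shown in Step 5, and the sponsor should accept that openly or revisit the target rate and sample size.

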#### Primary Outcomes Measure

Response by the Revised International Neuroblastoma Response Criteria and RECIST 1.1 guidelines at 1 month after completion of therapy (42, 43).

#### Secondary Outcomes Measures

Response by the Revised International Neuroblastoma Response Criteria and RECIST 1.1 guidelines at 4 months after completion of therapy.Progression-free Survival (PFS), defined as the time from registration until objective tumor progression or death or to date of censoring for patients who do not experience the event during trial follow-up.Overall Survival (OS), defined as the time from registration into the trial until date of death (death from any cause) or to date of censoring for patients who do not experience the event during trial follow-up.Hematological and renal toxicity according to CTCAE 5.0.

#### Sub Study Measures

Tumor and risk organ dosimetry (SPECT/CT), defined as the absorbed dose in Gray that the tumor sites and organs of risk receive following each administration of ^177^Lu-DOTATATE.Semi-quantitative analysis of the expression of SSTR-2 on immunohistochemistry in the primary tumor histology. The results will be correlated with tumor uptake on ^68^Ga-DOTATOC PET/CT.The uptake on ^68^Ga-DOTATOC PET/CT measured by SUV_max_ (maximum standardized uptake value). Pre-treatment SUV_max_ values will be correlated to the response to ^177^Lu-DOTATATE therapy.

### Planned Interim Analysis and Timelines

The two-stage design will ensure that the study is terminated after the first stage if there is insufficient evidence of therapeutic activity. If any unexpected severe adverse events (CTC grades 3, 4) are encountered, consideration will be given to suspending the entry of new patients pending clarification of a causal relationship, and the trial may be stopped if unacceptable toxicities are observed. An interim analysis will be performed after inclusion of the first 14 patients. The main analysis of all outcome measures is planned at 6 months after completion of treatment of the last patient. In addition, subsequent analysis of all survival outcome measures will be conducted 5 years after completion of treatment of the last patient.

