^177^Lu-DOTATATE targeting the SSTRs has been shown to be effective in the treatment of neuroendocrine tumors in adults. This type of tumor-specific radiation therapy, called peptide receptor radionuclide therapy (PRRT), has recently been established as second-line treatment for grade 1 and 2 midgut neuroendocrine tumors (NET), that progress after first-line treatment with octreotide (32). ^177^Lu-DOTATATE has been well-tolerated in adult patients with a low incidence of hematological and renal toxicity, which are the main reported side effects. Renal irradiation is compounded by proximal tubular reabsorption of the radiolabeled somatostatin analog and co-administration of amino acid solution has been shown to reduce the risk of renal damage, as has limiting the estimated cumulative radiation dose to the kidneys to 23 Gy or less. The administration of cationic amino acids saturates the renal tubular uptake of proteins/peptides and amino acids, thereby reducing the exposure to the radionuclide (33–35). Severe delayed complications such as secondary malignancies and renal insufficiency has been reported in adult cohorts, but in general, severe side effects are rare. Brabander et al. (36) found that 1.5% of patients developed myelodysplastic syndrome and 0.7% developed acute leukemia during a median follow-up of 5 years after Lu-DOTATATE treatment in a cohort of 610 patients. No therapy-related long-term renal or hepatic failure occurred. A study by Garske-Roman et al. (37) found similar frequencies in a cohort of 200 patients and a median follow-up of 31 months. In this cohort 4% of patients developed grade 2 and 0.5% grade 4 renal toxicity (30, 36, 37). In a recent report from the NETTER-1 Trial, 2% of 111 patients developed myelodysplastic syndrome, whereas no cases of acute myeloid leukemia were reported. One patient developed diffuse large B-cell lymphoma during long-term follow-up, deemed not related to the ^177^Lu-DOTATATE treatment. The long-term renal function was similar in treatment and control groups, but the number of evaluable patients was small (38).

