## Methods and Analysis

### Study Design and Setting

The LUDO-N Trial (EudraCT number: 2020-004445-36, ClinicalTrials.gov Identifier: NCT04903899) is a prospective, non-blinded, open-label, single arm two stage, multicenter phase II trial for pediatric patients between 18 months and 18 years old with relapsed or refractory high-risk neuroblastoma. Patients are recruited from the Nordic Society of Pediatric Hematology and Oncology (NOPHO) catchment area, including the Nordic countries and Lithuania, and from the Netherlands with a combined population of roughly 50 million. The LuDO-N Trial is sponsored by the Karolinska University Hospital (Stockholm, Sweden). Study centers have been established in each of the participating countries and the ^177^Lu-DOTATATE treatment will be given at the Karolinska University Hospital, Stockholm Sweden, the Princess Máxima Center, Utrecht, The Netherland and possibly at a later stage at the University College London Hospitals, London, UK. The trial aims to confirm the dose and assesses the response to ^177^Lu-DOTATATE (provided by Advanced Accelerator Applications, a Novartis company) as a single agent for treatment of relapsed or refractory high-risk NBL in children. The pediatric use of the Investigational Medicinal Product (IMP) ^177^Lu-DOTATATE, as well as non-IMPs SomaKit TOC® (^68^Ga-DOTATOC) and LysaKare® amino acid solution for renal protection, have been approved for the LuDO-N Trial by the European Medicines Agency (EMA). Competent authority and ethical approvals and are being applied for separately in each of the participating countries. Fourteen patients will be recruited in the first stage and provided a response, as defined by the Revised International Neuroblastoma Response Criteria (INRC) 1 month after completion of therapy, is seen in 3 or more of these patients, a further 10 will be enrolled in the second stage (42, 43). Accrual is expected to last for up to 60 months. Follow-up continues until 5 years after the last ^177^Lu-DOTATATE treatment or death, of all included patients, whichever occurs first. At writing, the LuDO-N Trial has opened for recruitment in Sweden and Norway and the first patient has recently received ^177^Lu-DOTATATE treatment within the trial.

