#### Secondary Study Objectives

To assess long term survival and response.To assess treatment-related toxicity.

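### The 5-year analysis is limited to survival, so haematological and renal toxicity is last analysed at the main analysis although patients are followed for 5 years

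*Protocol article*

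**What the plan says.** Under Planned Interim Analysis and Timelines, the protocol article dates two analyses after the interim look and gives each a scope. The first is broad: "The main analysis of all outcome measures is planned at 6 months after completion of treatment of the last patient". The second is narrower: "subsequent analysis of all survival outcome measures will be conducted 5 years after completion of treatment of the last patient".

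Toxicity is a secondary objective ("To assess treatment-related toxicity", Secondary Study Objectives). The matching outcome, "Hematological and renal toxicity according to CTCAE 5.0", stands in Secondary Outcomes Measures as an item separate from progression-free and overall survival, with no time window. It is therefore inside the first scope and outside the second.

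Study Design and Setting fixes the length of observation: "Follow-up continues until 5 years after the last ^177^Lu-DOTATATE treatment or death, of all included patients, whichever occurs first".

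The Introduction gives the reason to look late: "Severe delayed complications such as secondary malignancies and renal insufficiency has been reported in adult cohorts". For the largest adult cohort it cites, "1.5% of patients developed myelodysplastic syndrome and 0.7% developed acute leukemia during a median follow-up of 5 years".

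**The concern.** The article names late complications of this class of treatment, follows every patient long enough to see some of them, and then assigns the 5-year analysis to survival measures alone. Anyone following the text would tabulate toxicity for the last time when the most recently treated patients have been observed for only months, and would not return to it when follow-up is complete.

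What is at stake is the late-safety description for a schedule that the Discussion itself expects to carry more marrow toxicity. The Conclusion judges that benefits outweigh risks in these children. A toxicity summary that omits the later follow-up is a weaker basis for that judgement than the trial could provide at almost no extra effort.

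**Working it through.** The plan gives no figure on this point to reproduce. The check has two parts: how much of the planned follow-up comes after the last toxicity analysis, and how likely it is that a late marrow event falls there.

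**Inputs from the article**
- 24 patients if both stages are completed, 14 + 10 (Statistical Analysis Plan).
- Accrual of 3 to 5 years (Abstract, Results) and up to 60 months (Study Design and Setting), so A = 36 or 60 months.
- Main analysis 6 months after the last patient's treatment; follow-up capped at 60 months.
- Adult rates of 1.5% myelodysplastic syndrome and 0.7% acute leukaemia at a median follow-up of 5 years (Introduction).

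**Assumptions not in the article**
- Accrual is even.
- The two adult rates do not overlap, so they add to 2.2%. This is treated as a 5-year risk with constant hazard.
- Where deaths are allowed for, survival is exponential with a median of 12, 24 or 48 months.

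**Follow-up at the main analysis, no deaths**

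A patient treated u months before the last patient has min(6 + u, 60) months of follow-up.
- A = 36: range 6 to 42 months, mean and median 6 + 36/2 = 24. Nobody has reached 5 years. Later person-time is 24 × (60 − 24) = 864 of 24 × 60 = 1,440 patient-months, or 60%.
- A = 60: median 6 + 60/2 = 36. The earliest 10% of patients exceed the cap by 3 months on average, so the capped mean is 36 − 0.1 × 3 = 35.7. Two or three of the 24 have reached 5 years. Later person-time is 24 × (60 − 35.7) = 583 patient-months, or about 40%.

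**Chance of at least one marrow case after the main analysis, no deaths**

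Monthly hazard h = −ln(1 − 0.022)/60 = 0.000371. The chance is 1 − exp(−h × later patient-months).
- A = 36: 1 − exp(−0.000371 × 864) = 1 − exp(−0.320) = 27%.
- A = 60: 1 − exp(−0.000371 × 583) = 1 − exp(−0.216) = 19%.

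**The same with deaths**

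With λ = ln 2 / median survival and c the follow-up a patient could have at the main analysis, expected time at risk after it is (exp(−λc) − exp(−60λ))/λ. This is summed over 24 evenly spaced patients and divided by the expected total, 24 × (1 − exp(−60λ))/λ.

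| Assumed median survival | Share of person-time after main analysis, A = 36 | A = 60 | Chance of a later case, A = 36 | A = 60 |
|---|---|---|---|---|
| 12 months | 27% | 17% | 4% | 3% |
| 24 months | 42% | 27% | 10% | 7% |
| 48 months | 51% | 34% | 17% | 11% |

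Placing the first and last patients exactly at the ends of accrual moves these figures by about one percentage point at most.

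**The case against.** The best defence is that the article condenses a fuller protocol. The Secondary Study Objectives attach the long-term horizon to survival and response, not to toxicity. The Analysis section promises descriptive reporting of harms without a time limit. The adverse-event reporting period is left undefined, and the 5-year analysis is introduced as an addition, which need not exclude others. Late-safety tables could well sit in the full protocol. All of this limits what can be claimed. It does not remove the point, because the article is not silent here: it states the scope of the 5-year analysis, and that scope leaves toxicity out. If the full protocol provides a late toxicity analysis, this sentence misdescribes it and still needs correcting.

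Four stronger readings are tempting, and the article does not support them.
- A reader might infer that late toxicity goes uncollected. The article does not say so; the gap is in the planned analysis.
- A reader might take 6 months as the cohort's follow-up. It applies only to the last patient.
- A reader might quote 1 − (1 − 0.022)^24 = 41% as the chance of missing a case. That is the chance of any case over full follow-up with nobody dying. The part that falls after the main analysis is 19 to 27% without deaths, and lower with the poor survival that the Introduction and Conclusion describe.
- A reader might argue from the upper one-sided 95% limit for no cases in 24, 1 − 0.05^(1/24) = 11.7%. That shows 24 patients cannot characterise a rate near 2% even with complete follow-up, so it does not support the point.

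The renal evidence is also mixed. The Introduction reports no treatment-related long-term renal failure in the 610-patient cohort. Its grade 2 figure of 4% comes from a median of 31 months, which lies within the 24 to 36 months expected at the main analysis. The case for a late look therefore rests more on marrow events than on renal ones.

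**Conclusion.** The point holds as a badly chosen scope for one stated analysis. As written, toxicity is last analysed at the main analysis, and a material part of the follow-up already planned contributes nothing to it: about 40 to 60% of the 5-year person-time if nobody dies, or about 17 to 51% under assumed median survival of 12 to 48 months. The chance that a marrow malignancy falls in that unanalysed period is about 19 to 27% without deaths and roughly 3 to 17% with them.

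These figures depend on even accrual, completion of both stages, adult rates carried over to children, no overlap between the two rates, and constant hazard. Events clustering late would raise the chance; a stop after 14 patients would lower it. The consequence is confined to the late-safety description. It is worth correcting because the correction is cheap, not because the trial's main conclusion is at risk.

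**What to change.** Reword the 5-year sentence so that it covers all survival and toxicity outcome measures. At that analysis, report haematological and renal toxicity descriptively, together with any myelodysplasia, leukaemia or other second malignancy, and give the number of patients still alive and under observation so that a low count can be read against the time at risk. Simple counts and listings are enough for 24 patients. If the full protocol already plans this, state it in the article.

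The cost is one small descriptive analysis, and the recording of late toxicity at follow-up that is already planned. Sample size, the two-stage rule and patient management do not change.
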